## Abstract

**Background**: A sedentary behavior and being overweight represent major public health issues associated with both physical and psychological risks. Based on self-determination theory (SDT), the psychoeducational intervention PsicoFIT—a component of the TIGREFIT program—aims to foster motivation toward physical activity, to promote healthy habits, and to reduce psychological ill-being in sedentary adults who are overweight and are fans of a football club. **Methods**: This protocol corresponds to a longitudinal comparative pragmatic clinical trial, designed in accordance with the recommendations of the SPIRIT Statement. The intervention, preceded by a training program for the coaches involved, will comprise 12 weekly modules delivered in two modalities: (1) face-to-face, through group sessions, and (2) semi face-to-face, through short video capsules hosted on a digital platform. Changes associated with the intervention will be evaluated using hierarchical multiple regression and pre-post comparisons, assessing baseline and post-intervention data within and between the intervention modalities. Primary outcomes will include changes in healthy lifestyle and burnout as indicators of well-being and ill-being, respectively. Secondary outcomes will assess basic psychological needs satisfaction and autonomous motivation as potential mediators of these effects, as well as the coach’s controlling interpersonal style as a possible contextual predictor. The modality of participation will be analyzed as a potential moderator of the observed changes. Finally, the acceptability and perceived contribution of the intervention will be explored through a focus group. **Discussion**: PsicoFIT will provide a methodological framework for designing interventions within multicomponent programs aimed at promoting healthy lifestyles and psychological well-being in sedentary adults who are overweight, considering the social context of football fandom and allowing for an exploration of the impact of the face-to-face and semi-face-to-face modalities. Future empirical application of the protocol will help verify its effectiveness, guide adaptations across contexts, and contribute to the development of evidence-based interventions. **Conclusions**: The implementation of PsicoFit will allow for the evaluation of its effectiveness, psychological mechanisms, and delivery modalities, thus guiding future evidence-based interventions in sport.

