## 2. Materials and Methods

### 2.1. Design

A mixed-methods convergent parallel approach will be adopted [40] within the framework of a longitudinal comparative pragmatic clinical trial [41]. To examine changes and to compare delivery modalities, the participants will be randomly assigned to receive the intervention in either a face-to-face or semi face-to-face modality, with measurements at time 1 (baseline) and time 2 (post-intervention).

Quantitative analyses will include hierarchical multiple regression analyses, pre-post comparisons, and regression-based mediation and moderation analyses [42,43]. Additionally, the acceptability and perceived contribution of the intervention will be explored using a qualitative phenomenological approach [44] through a post-intervention focus group. The findings from the statistical analysis and the results of the phenomenological analysis will be integrated, allowing for a more precise understanding of the intervention’s evaluation, its perceived impact, and the acceptability of each modality.

Although this study does not constitute a controlled trial and does not include a no-intervention control group, to ensure methodological rigor and scientific transparency, it has been designed in accordance with the standard items of the SPIRIT 2013 Statement for clinical trial protocols [45] (see Supplementary Materials S1) and takes as a reference the elements of the Trials Registration Data Set (TRDS) [46] considered by the World Health Organization (WHO). In addition, the description of the intervention has been guided by the Template for Intervention Description and Replication (TIDieR) checklist [47] (see Supplementary Materials S2), with the aim of providing a comprehensive, transparent, and replicable account of the intervention components, delivery procedures, materials, and implementation context.

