#### 2.4.2. Football Fitness Training

The face-to-face modality includes, on a weekly basis, one hour of recreational training, two two-hour football-based exercise sessions, and 40 min of autonomous recreational physical activity.

The semi face-to-face modality also includes one hour of recreational training (face-to-face), two sessions averaging 24 min of high-intensity interval training (HIIT) through videos hosted through a digital platform, and 40 min of autonomous recreational physical activity per week.

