### 2.6. Data Analysis

#### 2.6.1. Quantitative Analysis

Due to the practical limitations in following up with those participants who do not complete the program, the primary analysis will be conducted using a per-protocol approach [111], considering only those participants with complete data at baseline and at the end of the intervention; missing data will not be imputed.

This approach will allow for evaluating the changes associated with each intervention under real-world implementation conditions, acknowledging the anticipated risk of participant attrition and that the benefits of randomization may not be fully preserved, while reflecting its applicability in a pragmatic context.

All statistical analyses will consider a 95% confidence level (5% error), ensuring transparency and reproducibility.

Preliminary Analysis. Descriptive statistics for central tendency (mean, median), dispersion (standard deviation and variance), and distribution (skewness and kurtosis) will be estimated for each observed variable. Next, normality tests will be conducted, and the reliability of the instruments will be estimated by measuring their internal consistency through Cronbach’s alpha (α) and McDonald’s omega (ω) coefficients. Subsequently, bivariate correlation analyses will be performed to measure the strength and direction of the relationship between the variables.

Associations among motivational and outcome variables. To examine the associations between the coach’s controlling interpersonal style, basic psychological need satisfaction, autonomous motivation, healthy lifestyle, and burnout, hierarchical multiple regression analyses will be conducted. Separate models will be estimated for each intervention modality (face-to-face and semi face-to-face) and for each measurement occasion (baseline and post-intervention), with predictor variables entered in a theoretically driven manner [42]. Effect sizes and confidence intervals will be calculated to complement the statistical significance, and statistical power will be considered when interpreting the results [112].

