Intervention-related changes. Changes in the coach’s controlling interpersonal style, basic psychological need satisfaction, autonomous motivation, healthy lifestyle, and burnout from baseline to post-intervention will be examined. Within-group pre-post comparisons will be conducted for each intervention modality (face-to-face and semi-face-to-face). Between-group comparisons will assess whether the magnitude of changes differs between the two modalities [42]. Effect sizes will be calculated to quantify the magnitude of the observed changes, and statistical power will be considered in interpreting the results [113].

Mediation effects. The effects of basic psychological needs satisfaction and autonomous motivation as mediating variables (the mediation effect of basic psychological needs satisfaction and autonomous motivation on the relationship between the coach’s controlling interpersonal style, healthy lifestyle, and burnout, as well as the effect of basic psychological needs satisfaction on the relationship between autonomous motivation, healthy lifestyle, and burnout) will be evaluated using regression-based mediation analyses with bootstrapping procedures to estimate direct and indirect effects following Hayes’s recommendations [43], considering pre- and post-intervention data. The significance of mediation inferred when the confidence interval of the indirect effect does not include zero allows for the assessment of whether the observed relationships are explained directly or indirectly through the proposed mediating variables. Mediation effects will be considered exploratory due to the sample size and the nature of the study.

Moderation Effects. The moderating effects of both intervention modalities will be evaluated using regression-based moderation analyses, following Hayes’s recommendations [43], considering both pre- and post-intervention data. Moderation will be examined by including interaction effects, as evaluated through bootstrapped confidence intervals. Significant interaction effects will indicate that the strength or direction of the relationship between predictors and outcomes differs according to the intervention modality. Moderation effects will be considered exploratory due to the sample size and the nature of the study.

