The integration of this protocol within a broader program that includes three interventions and a coach training component implies that observed changes in the study variables may be influenced by the effects of other interventions. While efforts will be made to isolate the specific impact of the present intervention, the results may reflect interactions among different program components, although this problem can also be mitigated to some extent by including it within the same theoretical framework of self-determination, since theoretical coherence could ensure that the strategies, language, and techniques used, as well as the objectives, are consistent, facilitating implementation, acceptance by the participants, and maximizing the potential results [123]. Finally, it should be noted that the results are limited in their generalizability due to the nature of the participants: all of them are football fans, as well as the difference in the “dose” of the intervention between the modalities, which could influence comparative outcomes.

Based on everything discussed and the limitations expressed, it seems clear that the most relevant future development is the empirical application of the protocol in the most efficient way possible, as well as presenting the results obtained, to be replicated for verification and eventual validation as a useful psychoeducational intervention to meet the stated objectives.

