## 4. Conclusions

This article presents the PsicoFIT psychoeducational intervention protocol, grounded in Self-Determination Theory, which aims to promote healthy lifestyles and psychological well-being among overweight sedentary adults who are fans of a football club. The detailed description of its theoretical foundation, structure, implementation, and evaluation plan seeks to provide methodological guidance for the development of future interventions integrating psychological and behavioral approaches in sport-related contexts. The future empirical implementation of this protocol will allow for the analysis of its effectiveness, the psychological mechanisms involved, and the usefulness of its different delivery modalities.

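### The article says the trial will evaluate PsicoFIT's effectiveness and try to isolate its impact, but no planned comparison can do either: both arms receive PsicoFIT and the modalities differ across the whole TIGREFIT package

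*Protocol article*

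**What the plan says.** **Claims.** The Abstract ends with "The implementation of PsicoFit will allow for the evaluation of its effectiveness, psychological mechanisms, and delivery modalities". Section 4 says that carrying out the protocol "will allow for the analysis of its effectiveness". The research objectives in section 1 describe the overall goal as examining changes that result from the psychoeducational intervention. On the other programme components, section 3 says: "While efforts will be made to isolate the specific impact of the present intervention".

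**Design.** Section 2.1 randomises participants to a delivery modality and states that "this study does not constitute a controlled trial and does not include a no-intervention control group". Section 2.5 gives all twelve PsicoFIT modules to both arms. Section 2.4 applies the modality to the whole multicomponent programme. The face-to-face arm has "two two-hour football-based exercise sessions" each week where the other arm has two short video HIIT sessions (2.4.2), and nutrition content differs as well (2.4.3).

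**Analysis.** Under section 2.6.1, "Within-group pre-post comparisons will be conducted for each intervention modality", and the size of the change is also compared between modalities. Section 2.6.1 sets one error level throughout: "All statistical analyses will consider a 95% confidence level (5% error". Section 2.7.1 names two primary outcomes, healthy lifestyle and burnout, each as post-intervention minus baseline. Only mediation and moderation are labelled exploratory.

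**The concern.** To say that PsicoFIT is effective, the trial needs a comparison in which PsicoFIT is what differs. Here the randomised factor is how the whole programme is delivered, and PsicoFIT is present on both sides.

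Two results would then be open to misreading. A significant pre-post change in an arm, which Hypothesis 2 expects, could be reported under the heading of effectiveness although it cannot be attributed to PsicoFIT. A difference between modalities could be reported as the effect of PsicoFIT's format although exercise and nutrition differ at the same time. The Abstract and Conclusions are where the claim is strongest, and they are the parts most often read and cited.

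**Working it through.** The article gives no figure to reproduce on this point. The sample of 80 rests on feasibility (2.2.4), with no effect size, SD or power.

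**Step 1. What each planned comparison can estimate.**

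| Comparison (2.6.1) | What it contains | Gives a PsicoFIT effect? |
|---|---|---|
| Pre-post, face-to-face arm | PsicoFIT + exercise + nutrition + coach training + time | No |
| Pre-post, semi face-to-face arm | The same components in their other format | No |
| Change, face-to-face versus semi face-to-face | Package versus package | No; PsicoFIT is in both arms |

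**Step 2. What differs between the arms.** Scheduled minutes per week, from 2.4.2, 2.4.3 and 2.5:

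| Component | Face-to-face | Semi face-to-face | Difference |
|---|---|---|---|
| Exercise | 60 + 2×120 + 40 = 340 | 60 + 2×24 + 40 = 148 | 192 |
| Nutrition | 30 (plus counselling, not timed) | 5 | 25 |
| PsicoFIT | 30 | 5 | 25 |
| Total | 400 | 158 | 242 |

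PsicoFIT is 25/242 = 10% of the scheduled difference and exercise is 192/242 = 79%. The 158 assumes that the nutrition capsules are weekly; 2.4.3 says only that there is a series. The recreational hour, the 40 minutes of autonomous activity, coach training and Module 9 are common to both arms. Minutes do not measure influence on a psychological outcome. The table shows only that the contrast is not one of PsicoFIT format alone.

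**Step 3. The article against itself.** Section 2.1 says the study is not a controlled trial. Section 2.3.1, on burnout, accepts that changes cannot be attributed to the psychoeducational part alone. Section 3 concedes influence from the other interventions and unequal dose between modalities. None of these fits with an evaluation of PsicoFIT's effectiveness. Section 2.6 contains no element that would isolate its impact, and no analysis of these two arms could supply the missing comparator.

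**Step 4. Error rate for the two primary between-modality contrasts.** At 5% each, unadjusted:
- upper bound: 2 × 0.05 = 0.10;
- if independent: 1 − 0.95² = 0.0975.

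**Step 5. Cost of controlling it.** Under Holm the smaller p-value must be at most 0.05/2 = 0.025. By the normal approximation, the standardised difference detectable with 80% power is (z₁₋α/₂ + z₀.₈) × √(2/n):
- n = 40, α = 0.05: (1.960 + 0.842) × 0.2236 = 0.63;
- n = 40, α = 0.025: (2.241 + 0.842) × 0.2236 = 0.69.

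The exact two-sample t calculation gives 0.634 and 0.701. With 32 per arm (an assumed 20% attrition; the article gives no rate), the t values are 0.71 and 0.79.

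**The case against.** **The limits are disclosed.** Sections 2.1, 2.3.1 and 3 state most of the attribution problem, and 2.6.1 speaks of changes associated with the intervention. This stands, and it narrows the fault to claims that exceed the design. It does not remove it: the Abstract and Conclusions keep the effectiveness wording, and section 3 adds a promise with no method behind it.

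**Change is not judged within arms only.** A comparison between randomised modalities is planned. This also stands, and that contrast is the most useful one in the trial. It still compares packages.

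**Regression to the mean.** A reader might infer that selecting people with under 150 minutes of weekly activity makes an apparent gain in the lifestyle score likely with no effect at all, and put a size on it. The documents do not support that. Such a figure requires selection on the same baseline score that enters the paired test. Eligibility is screened at enrolment on reported activity (2.2.2, 2.2.3, Table 1), while the lifestyle survey is a different instrument with ten factors, given later at week 0 (2.3.1, 2.3.3). Burnout is not a selection variable.

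**Multiplicity.** A reader might multiply five constructs by three comparisons and quote a very high false-positive rate. That treats overlapping tests on the same participants as independent, and an analysis plan that is not shown may hold a testing rule. What remains is modest: the article itself applies 5% to all analyses and has two primary outcomes.

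**Conclusion.** The point holds as a mismatch between claim and design. The trial can estimate how change differs between two TIGREFIT packages, and it can describe change within each. It cannot estimate PsicoFIT's effect or the effect of PsicoFIT's format, because no comparison isolates either. This follows from the stated design and needs no assumption about effect sizes.

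The randomised contrast carries its own caveat. Section 2.6.1 restricts the primary analysis to participants with complete data and concedes that the benefits of randomisation may not be fully kept.

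Multiplicity is secondary: up to about 10% familywise error over the two primary contrasts if each is tested at 5%. Adjusting alpha would do nothing for attribution. It would be wrong to conclude that the authors are unaware of the limits, or that within-arm tests are the only evidence planned.

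**What to change.** 1. In the Abstract, the research objectives (overall goal, Objective 2, Hypothesis 2), section 2.6.1 and section 4, state the main question as the comparison of change between the face-to-face and semi face-to-face TIGREFIT packages on healthy lifestyle and burnout.
2. Report within-arm changes as estimates with confidence intervals, and make no effectiveness claim for PsicoFIT from them.
3. Delete the promise in section 3 to isolate PsicoFIT's specific impact.
4. State beside the main question that analysing completers only weakens the randomised contrast.
5. Test the two primary between-modality contrasts with Holm at an overall 5%, and label the remaining tests secondary or exploratory.

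**Cost.** No extra participants, visits or data. It is slightly more than wording, because Objective 2 and Hypothesis 2 change in emphasis; section 2.8 sends substantial modifications to the ethics committee, so the investigators should judge whether this is one. The claim becomes narrower, and the detectable difference for the smaller p-value rises from about 0.63 to 0.70 SD at 40 per arm with 80% power, more with attrition.

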## 1. Introduction

A sedentary lifestyle and being overweight constitute major public health concerns affecting a substantial proportion of the adult population worldwide [1,2], and these conditions are closely interrelated [3,4]. Sedentary behavior, predominantly characterized by insufficient engagement in physical activity [5,6], contributes to excess body weight [4], which in turn creates barriers to adopting and maintaining an active lifestyle [7,8,9]. This reciprocal relationship often results in a self-perpetuating cycle with detrimental consequences for both physical health [1,5,10] and psychological well-being [11,12,13,14,15,16].

By contrast, regularly engaging in physical activity has been consistently identified as a protective factor for promoting improvements in physical health and for multiple indicators of psychological well-being [5]. However, initiating and sustaining healthy habits remains particularly challenging among sedentary and overweight populations, where a lack of motivation or behavior regulation primarily driven by external factors often predominates [17,18,19,20].

Self-determination theory (SDT) provides a robust theoretical framework for understanding the motivational processes underlying health-related behavioral change [20,21]. SDT conceptualizes motivation along a continuum, ranging from controlled to autonomous regulation, and emphasizes the role of social and contextual factors in facilitating personal growth and well-being through the satisfaction of three basic psychological needs: autonomy (freedom to choose actions, set goals, and make decisions), competence (sense of achievement and effectiveness in interacting with the environment), and relatedness (maintaining meaningful social connections and a sense of belonging to a community).

From an SDT perspective, well-being is conceptualized in eudaimonic terms, reflecting the individuals’ active engagement in personal development, goal pursuit, and the realization of their potential [20]. Well-being therefore encompasses multiple lifestyle-related domains, including physical activity, adequate rest, balanced nutrition, positive interpersonal relationships, and a sense of life purpose [22].

Autonomous motivation plays a central role in the adoption and maintenance of health-promotion behaviors by facilitating sustained engagement and behavioral persistence [20]. Previous research has shown that autonomous motivation is nurtured by the satisfaction of basic psychological needs and is positively associated with indicators of psychological well-being and healthy lifestyles [20,21,23,24].

According to SDT, less autonomous forms of motivation are associated with higher levels of ill-being [20,21]. Burnout, characterized by a reduced sense of accomplishment, devaluation of the activity, and emotional and physical exhaustion [25,26], has been recurrently framed in sports contexts as an indicator of ill-being. Drawing on this conceptualization, these dimensions may also plausibly manifest in individuals seeking to initiate or to maintain physical activity for health and well-being. The evidence suggests that motivation quality is a relevant predictor of changes in burnout, with lower autonomous motivation typically preceding higher levels of burnout [27,28].

SDT further highlights the importance of support from authority figures to foster autonomous motivation [29], as exemplified by coaches in physical activity settings, through the interpersonal style they adopt in interacting with participants. Research shows that controlling interpersonal styles, characterized by pressures to think, feel, or behave in specific ways, and a disregard for the participants’ interests and perspectives negatively impact autonomous motivation by undermining the satisfaction of basic psychological needs [20,21,30,31,32]. The coach’s interpersonal style is therefore a key contextual factor in comprehensive programs targeting physical activity and well-being.

SDT-based interventions have demonstrated effectiveness in promoting healthy behaviors and psychological well-being among adult populations though both face-to-face and remotely delivered formats. These programs typically include motivational support strategies and health education, and have been shown to enhance autonomous motivation, physical activity engagement, and indicators of well-being.

For example, McDonough et al. [33] reported improvements in autonomous motivation, physical activity, and sleep quality following a 12-week remote intervention for inactive adults using exercise videos and guidance on exercise and sedentary behavior risks, combined with strategies to promote an active lifestyle. Similarly, Dean et al. [34] observed increased physical activity and reductions in body weight following a 10-week program for overweight or obese men combining in-person sessions, activity monitoring, and informational and motivational messages.

Taken together, this body of evidence supports the usefulness of SDT-based interventions for promoting physical activity and psychological well-being in adults. In light of this evidence, it appears pertinent to develop and describe theoretically grounded intervention protocols that explicitly operationalize SDT principles and examine their application across different delivery modalities, including face-to-face and remotely formats.

From an applied perspective, football clubs have been identified as potentially promising settings for the development of initiatives aimed at promoting health and well-being among their supporters, mainly due to their capacity to facilitate recruitment and to provide accessible and socially attractive environments for the implementation of intervention programs [35,36,37,38].

Within this context, TIGREFIT [39] was developed as a multicomponent lifestyle program targeting sedentary and overweight supporters of the professional Mexican football club, Club Tigres, integrating physical training, nutritional guidance, and psychoeducational intervention delivered in the face-to-face and semi face-to-face modalities, along with prior coach training aimed at supporting a motivational approach consistent with the program’s conceptual framework.

PsicoFIT constitutes the psychoeducational component of the TIGREFIT program and was designed to promote motivation toward physical activity and psychological well-being, while reducing indicators of ill-being. The intervention is grounded in SDT and in empirical evidence linking the coach’s interpersonal style, satisfaction of basic psychological needs, and autonomous motivation with key psychological outcomes in physical activity contexts. Accordingly, PsicoFIT was conceptually structured to support autonomy, competence, and relatedness through a progressive psychoeducational approach, providing the theoretical basis for both the intervention design and the evaluation plan.

